### Who will take informed consent? {26a}

The study staff will conduct informed consent via telephone. Eligible families will provide consent (parents) and assent (adolescents) verbally and in writing using online forms via the Research Electronic Data Capture system (REDCap) [22].

### Additional consent provisions for collection and use of participant data and biological specimens {26b}

N/A: There are no ancillary studies. This trial does not involve collecting biological specimens.

### Interventions

#### Explanation for the choice of comparators {6b}

Adolescents assigned to the control condition in treatment phase 1 receive access to a sleep education website (Sleep EDU) that was developed for this study. The education materials are delivered in six treatment cores, designed to be completed once per week over 6 weeks. The program is metered so that adolescents complete one core per week. Parents receive three email messages (one every 2 weeks) with a summary of the information provided in the adolescent program. The education materials do not include any instruction in cognitive or behavioral skills for insomnia. The content was compiled from publicly available educational websites about sleep (e.g., Kids Health, Sleep Foundation, American Academy of Sleep Medicine). The purpose of this comparator condition is to control for time, attention, and Internet usage and to allow masking of treatment allocation. In our prior RCTs using similar online patient education control conditions, youth and parents have shown a high level of engagement and high ratings of treatment credibility [16].

#### Intervention description {11a}

##### CBT-Insomnia intervention

Adolescents assigned to CBT-I in treatment phase 1 receive access to the Firefly website, an interactive, self-guided intervention that delivers the core components of CBT-I for adolescents. Firefly was adapted from face-to-face CBT-I for adolescents with insomnia and comorbid physical and mental health conditions and Internet-delivered CBT-I for adults [14, 15, 23, 24]. Firefly includes six treatment cores: (1) introduction to the intervention and goal setting, (2) sleep restriction, (3) stimulus control, (4) cognitive skills for sleep, (5) sleep hygiene, and (6) relapse prevention and maintenance. Firefly includes a daily sleep diary which is used to generate tailored recommendations for sleep restriction. Consistent with the core principles of CBT-I, the overarching goal of treatment is to develop a consistent sleep-wake schedule and strengthen the association between bed and sleep by limiting time awake in bed.

Firefly is metered so that adolescents complete one core per week. Each core includes interactive features to deliver skills training including animations, games, quizzes, and vignettes of peers. At the end of each core, adolescents review their knowledge with brief quizzes and then receive an assignment corresponding with the skills taught in the core (e.g., follow their recommended sleep schedule for sleep restriction, set up a nesting place for stimulus control). Youth are asked to practice the skills in each assignment and complete their daily sleep diary for 7 days, until the next core is released. To support engagement, automated emails are sent when it is time to complete a new treatment core, to enter sleep diaries, and to encourage the completion of homework assignments. See Fig. 3 for screenshots of the Firefly program.

**Fig. 3 Fig3:**
[figure not shown]
Screenshots from the Firefly website showing **a** home screen, **b** daily sleep diary, **c** skills practice, and **d** peer vignettes

At the beginning of each new core, adolescents report on their experience with the assignment from the prior core and receive tailored recommendations to address barriers and support continued skills practice. Adolescents who have completed at least 5 sleep diaries in the past week also receive personalized recommendations for sleep restriction, which are computed automatically using algorithms developed for the Firefly program with a goal to reach > 85% sleep efficiency with a sleep duration of 9–10 h per night on average. Adolescents who complete fewer than 5 sleep diaries during a given week can move forward when the next core is released but are not provided new recommendations for sleep restriction. Firefly is designed to be completed in 6 weeks. After completing the final core, adolescents can choose to continue using Firefly to monitor their sleep, receive personalized recommendations for sleep restriction, and practice skills as long as they desire.

Consistent with face-to-face CBT-I for adolescents, parents participate in a supportive role and receive a series of 3 email messages (one every 2 weeks) that provide information about the cognitive and behavioral insomnia skills their teen is learning in Firefly and instruction in supporting their teen in using the program and implementing the skills they are learning.

##### CBT-Pain intervention

Treatment phase 2 begins 2–3 weeks after completion of treatment phase 1. In treatment phase 2, all adolescents and parents receive access to WebMAP, an established Internet-delivered CBT-Pain intervention for youth with chronic pain. WebMAP has demonstrated small to moderate treatment effects for improving pain-related disability in multiple clinical trials of youth with chronic pain conditions [16, 17]. WebMAP is guided by cognitive-behavioral, social learning, and family system frameworks [25]. Adolescents and parents access separate versions of the program. The adolescent version of the program includes six treatment cores: (1) pain education and goal setting, (2) cognitive skills for pain management, (3) relaxation methods, (4) coping with pain outside the home, (5) healthy habits, and (6) relapse prevention and maintenance. The parent version of the program also includes six cores: (1) pain education and goal setting, (2) family resilience strategies, (3) operant training, (4) communication skills, (5) modeling and self-care, and (6) relapse prevention and maintenance.

WebMAP is metered so that adolescents and parents complete one core per week. Interactive features include animations, games, quizzes, audio files of relaxation exercises, and video and story vignettes of adolescents and parents coping with pain. At the end of each core, users review their knowledge with brief quizzes and then receive an assignment corresponding with the skills taught in the core (e.g., practice relaxation methods using the audio files). Youth and parents are asked to practice the skills in each assignment for 7 days, until the next core is released. For more details about WebMAP, please see our prior publications [16, 17, 26].

#### Criteria for discontinuing or modifying allocated interventions {11b}

Participants can discontinue the trial procedures and request to be removed from the trial at any time. Study investigators can discontinue a patient’s participation in the study if they do not complete the pre-randomization/baseline assessment, or upon new presentation of exclusion criteria (e.g., inpatient hospitalization, diagnosis of a new serious medical condition). Data that have been collected prior to discontinuation will be included in analyses. This is a low-risk behavioral trial, and adverse events are expected to be minor; therefore, there are no planned criteria for premature study termination or for modifying allocated interventions.

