### Eligibility criteria {10}

We will use a two-stage eligibility screening process. Providers in the Seattle Children’s Hospital Neurology Clinic will identify patients who are 11–17 years old with migraine and self-reported sleep difficulties. Providers will give families a study brochure and submit their contact information to the study team via a secure internal message in the hospital’s electronic health record after obtaining verbal permission to do so from the parent. After receiving referral information, the study staff will contact the families via telephone to conduct a second stage of eligibility screening with the adolescent and parent based on the criteria below. Eligibility criteria were informed by the American Headache Society (AHS) guidelines for trials of behavioral treatments for pediatric headache [18].

Adolescents must meet the following criteria to be eligible for enrollment:Age 11–17 years.Diagnosis of migraine with or without aura or chronic migraine without continuous headache, as defined by the International Classification of Headache Disorders 3rd Edition (ICHD-3) [19] by the referring provider in Neurology Clinic.Meets the research diagnostic criteria for insomnia disorder (self-reported sleep difficulties 3 or more nights during the past month with at least one daytime sleep-related problem) [20].Score on the Pediatric Migraine Disability Assessment scale (PedMIDAS) greater than 10, indicating at least mild headache-related disability [21].Headache frequency of 6 or more days per month [18].Access to the Internet on any web-enabled device.Adolescents on a stable dose (× 2 months) of prophylactic medications for migraine or sleep (antidepressants, anticonvulsants, supplements, etc.) will be eligible.

Adolescents who meet any of the following criteria will not be eligible for enrollment:Adolescent or parent cannot read in EnglishHas another primary sleep disorder (e.g., sleep apnea, narcolepsy) or an unusual sleep/wake schedule or circadian rhythm disorderIs currently experiencing a psychiatric crisis (e.g., active suicidality, psychosis)Received psychological therapy for insomnia or pain in the 6 months prior to screening

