#### Relevant concomitant care permitted or prohibited during the trial {11d}

For the duration of the trial, all participants will continue standard care in the neurology clinic. Participants can engage in any other intervention or treatment (e.g., counseling, massage therapy, acupuncture, medication management) as recommended by their care providers. We will collect information on concomitant therapies received during the trial via participant self-report.

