#### Plans to promote participant retention and complete follow-up {18b}

Participants will receive detailed information about the study protocol during recruitment and enrollment and will receive emails, text messages, and telephone reminders from the study staff to complete follow-up assessments. Participants will also be provided with an e-commerce gift card after completing each assessment. Questionnaire measures and daily diaries are completed online so that participants can complete these at a time and place that is convenient for them. All survey responses are saved so that participants do not have to complete questionnaire measures in a single sitting. All participants will be invited to complete follow-up assessments, including those who do not complete the intervention.

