### Methods in analysis to handle protocol non-adherence and any statistical methods to handle missing data {20c}

Primary analyses will be intent-to-treat analyses, which will include all participants randomized regardless of intervention completion. Missing data will be minimized to the extent possible using the methods described above. If needed, for multi-item instruments, missing data at the item level will be addressed using published guidelines where available. For primary and secondary outcome analyses, the amount of missing data and pattern of missing data will be examined. If a substantial amount of missing data exists, in addition to our primary data analysis using all available data, we will conduct additional sensitivity analysis using multiple imputations with changed equations.

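### Investigators may end a randomised participant's study participation for events that are not on the exclusion list, and the rule implies that outcome assessment stops, which conflicts with the promise to invite everyone to follow-up

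*Protocol article*

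**What the plan says.** Protocol article, section {11b}, gives two grounds on which investigators may act. The first is "Study investigators can discontinue a patient’s participation in the study if they do not complete the pre-randomization/baseline assessment". The second is "or upon new presentation of exclusion criteria (e.g., inpatient hospitalization, diagnosis of a new serious medical condition"). On data, the section says: "Data that have been collected prior to discontinuation will be included in analyses".

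Section {10} lists four exclusions:
- the adolescent or parent cannot read English;
- another primary sleep disorder, an irregular sleep schedule or a circadian disorder;
- "currently experiencing a psychiatric crisis (e.g., active suicidality, psychosis");
- "Received psychological therapy for insomnia or pain in the 6 months prior to screening".

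Two other sections bear on what happens after a participant stops. Section {18b}: "All participants will be invited to complete follow-up assessments, including those who do not complete the intervention". Section {20c} describes the primary analyses as intent-to-treat, "which will include all participants randomized regardless of intervention completion", carried out on all available data, with multiple imputation as an added sensitivity analysis if much is missing. Section {11d} says of concomitant care: "Participants can engage in any other intervention or treatment (e.g., counseling, massage therapy, acupuncture, medication management").

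**The concern.** The second ground in {11b} refers back to the exclusion list but illustrates it with events that the list does not contain. A reader cannot tell which events count, and the rule is permissive, so its use is left to discretion.

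What ends is participation in the study, not only use of the web program. If outcome assessment ends too, the trial loses post-randomisation outcomes for health events. Those events may plausibly be related to activity limitation (CALI-9) and sleep (ISI): a hospital stay or serious illness can affect both. This link is an inference; the protocol does not state it. If the losses differ between arms, the treatment comparison can shift. If they do not differ, the cost is mainly precision.

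**Working it through.** **1. Does the rule reach randomised participants?** Under section {16c}, allocation follows the pre-treatment assessment, so the incomplete-baseline ground acts before randomisation. The second ground has no time limit and stands in a section about allocated interventions, so it applies after randomisation.

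**2. Do the examples match the list?** Neither inpatient hospitalisation nor a new serious medical condition is one of the four exclusions. A psychiatric crisis could lead to admission, but the exclusion names the crisis and not the admission. Read literally after randomisation, the prior-therapy exclusion would also sit badly with {11d}, which permits other treatment, including counseling.

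**3. Do {11b} and {18b} agree?** {11b} ends study participation and speaks only of data gathered beforehand. {18b} invites all participants to follow-up and makes no exception for investigator discontinuation. On the natural reading, both cannot apply to the same person.

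**4. What happens to the primary sleep comparison?** Section {20a} compares ISI at phase 1 post-treatment by t-test and covariate-adjusted regression. Someone removed before then has no post-treatment ISI. Retained baseline data can enter the mixed model but do not supply that value.

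**5. The plan's own sample size.** Inputs from section {14}: d = 0.45, 80% power, 77 per group, 15% attrition, 180 enrolled, 154 final. Two-sided alpha of 0.05 is assumed, because the article does not state it.
- n per arm = 2(1.960 + 0.842)² / 0.45² = 77.5, rounded up to 78, against 77 stated. Power at 77 per arm is 79.7%.
- 154 / (1 − 0.15) = 181.2, rounded up to 182, against 180 stated. 180 × 0.85 = 153.

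These agree within rounding and are not in dispute.

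**6. Illustrated shift in the effect.** Let q₁ and q₀ be the fractions removed in the two arms, and g the gap in SD by which removed participants are worse than those retained. Each full-arm mean is worse than its retained mean by q × g, so the observed contrast shifts by (q₁ − q₀) × g. The rates and gaps are assumed, because the documents give none.

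| Between-arm difference in removal | g = 0.5 SD | g = 1 SD |
|---|---|---|
| 0 points | 0 | 0 |
| 3 points | 0.015 SD (3%) | 0.03 SD (7%) |
| 5 points | 0.025 SD (6%) | 0.05 SD (11%) |
| 10 points | 0.05 SD (11%) | 0.10 SD (22%) |

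Percentages are shares of d = 0.45; for example, 0.05 / 0.45 = 11%. The direction depends on which arm loses more: greater removal from the CBT-I arm flatters CBT-I, and greater removal from the control arm understates its effect.

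**7. Illustrated loss of power.** Suppose removals come on top of the 15% attrition. Then n per arm = 180 × (0.85 − x) / 2.
- x = 0: 76.5 per arm, power 79.5%
- x = 2%: 74.7 per arm, power 78.5%
- x = 5%: 72.0 per arm, power 77.0%
- x = 10%: 67.5 per arm, power 74.4%

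If the 15% already covers such removals, there is no further loss.

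**The case against.** Several stronger readings are tempting, and the documents do not support them.

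- **That {11b} flatly contradicts intent-to-treat.** {20c} analyses all available data, and {11b} keeps what was collected before discontinuation. Participants can stay in their randomised arm with the data they have. A missing ISI after removal is a missing-data problem, as for any dropout. It weakens the intent-to-treat aim but does not make the statements incompatible.
- **That {11b} forbids later assessments.** It says that earlier data will be used; it does not say that later data will not be collected. The stop is implied by ending study participation and by silence on what follows. {18b} could also be read as addressing mainly those who leave the intervention. That reading eases the conflict but still leaves no rule for a participant whom the investigators discontinue.
- **That harm follow-up is cut short.** Section {22} continues monitoring after withdrawal or discontinuation for a serious adverse event, until the problem has resolved or stabilised or is found unrelated. Hospitalisation is a likely candidate for that provision.
- **That bias is shown in both primary outcomes.** No event rate is given, and the interventions are described as low risk. Under {17a} investigators are blinded, which makes a markedly one-sided pattern of removal less likely. Blinding is not complete, since {17b} lets them learn the assignment after an adverse event. Exposure also differs by outcome: ISI is compared within weeks of randomisation, while the whole course runs just over 9 months (6 weeks + 2–3 weeks + 6 weeks + 6 months).

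What stands against all of this is narrower: the examples do not match the list, and {11b} and {18b} leave the status of a discontinued participant unresolved.

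**Conclusion.** The point holds in limited form and is worth correcting. Two things follow from the text alone: the named events are not on the exclusion list, and ending study participation conflicts with the invitation of all participants to follow-up. That outcome collection stops, and that the events relate to outcome, are reasonable inferences and not stated facts.

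The size is unknown. It is nil for bias if removal is equal between arms in the simple model, and probably small if such events are rare. It reaches 6% to 11% of the planned effect only under an assumed 5-point imbalance with removed participants 0.5 to 1 SD worse.

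**What to change.** Amend section {11b} in two respects.

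1. Reconcile the events it names with the exclusion list in {10}, and with the concomitant care allowed in {11d}. Which events belong there is for the clinical team; no view is taken here.
2. Separate stopping the web program from stopping assessment. State that neither stopping the program nor discontinuation by the investigators by itself ends outcome assessment. Randomised participants stay invited to the remaining assessments unless consent or assent is withdrawn or the clinical team judges assessment inappropriate, and their data are analysed in the randomised arm. {18b} and {20c} can then refer to this rule.

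The cost is a short amendment and a few extra assessments. Under section {18a}, questionnaires and diaries are completed online and the actiwatch travels by post, so no visits are added.

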#### Strategies to improve adherence to interventions {11c}

The study staff will interact with participants regularly via text message, email, and telephone to communicate study procedures, encourage program completion, and address general questions and technical issues. Automated email reminders in the Firefly and WebMAP programs will also promote adherence to the intervention. Analytics will be used to track participants’ logins and module completion in the web programs.

#### Relevant concomitant care permitted or prohibited during the trial {11d}

For the duration of the trial, all participants will continue standard care in the neurology clinic. Participants can engage in any other intervention or treatment (e.g., counseling, massage therapy, acupuncture, medication management) as recommended by their care providers. We will collect information on concomitant therapies received during the trial via participant self-report.

#### Provisions for post-trial care {30}

Adverse events are expected to be minor. Therefore, there are no provisions for any additional ancillary or post-trial care or to provide compensation to those who suffer harm from trial participation.

### Outcomes {12}

The primary outcome following treatment phase 1 is change in self-reported insomnia symptoms (Insomnia Severity Index (ISI) [27]) from pre-randomization/baseline to immediately after treatment phase 1, immediately after treatment phase 2, and 6-month follow-up. The ISI has shown strong validity and reliability estimates, including sensitivity to change in response to insomnia treatment for teens with physical and mental health comorbidities [14, 15]. Secondary outcome measures of sleep include self-reported sleep quality (Adolescent Sleep-Wake Scale-Short Form (ASWS-SF)) [28] and sleep patterns (sleep duration, sleep efficiency, and wake after sleep onset) assessed using 14 days of daily sleep diary and actigraphic monitoring (Actiwatch Spectrum Plus, Phillips Respironics, Bend, OR) [29, 30].

The primary outcome following treatment phase 2 is change in activity limitations due to headache (Child Activity Limitations Interview-9 (CALI-9)) [31] from baseline to phase 1 post-treatment, phase 2 post-treatment, and 6-month follow-up. The CALI-9 measures difficulty in performing usual daily physical, social, and recreational activities (e.g., going to school, participating in activities at home) due to headache and has demonstrated sensitivity to change in response to CBT-pain treatment. Adolescents will complete a 14-day electronic diary which includes (1) the CALI-9 diary version [32], (2) the presence of headache (yes/no) to compute headache frequency [33] (secondary outcome), and (3) headache pain intensity (11-point Numerical Rating Scale (NRS)) [34] (secondary outcome). Additional secondary outcomes include self-reported emotional functioning (PROMIS Pediatric Anxiety and Depression short form scales v.2.0) [32] and health-related quality of life (youth self-report Pediatric Quality of Life Inventory 4.0) [35].

Adolescents and parents will complete a Treatment Experience Survey adapted for this study [36] concerning whether they experienced negative effects of study participation (e.g., worrying about sleep or pain, overwhelmed with treatment assignments, tension at home) and rate the level of discomfort experienced (0 = did not affect me/my teen at all, 3 = affected me/my teen very negatively). The number, type, and severity of negative experiences will be summarized. Participants will also report adverse events via free text response at each assessment time point.

